## Abstract

**Background::**

Cerebral palsy (CP) is a neurodevelopmental disorder caused by a brain injury resulting in poor coordination and motor control deficits, which is one of the most common physical disabilities in children. CP brings a heavy burden on families and society and becomes a significant public health issue. In recent years, hydrotherapy, and transcranial direct current stimulation (tDCS) as a physical therapy for CP is developing rapidly. When hydrotherapy and tDCS are used to treat separately, it has positive therapeutic effect in children with CP. The development of new therapies in combination with physical rehabilitation approaches is critical to optimize functional outcomes. tDCS has attracted interest in this context, because of significant functional improvements have been demonstrated in individuals with brain injuries after a short period of cerebral stimulation. Since the onset of this work, tDCS has been used in combination with constraint-induced therapy, virtual reality therapy to potentiate the treatment effect. Up to now, there are no studies on the effect of a combined application of hydrotherapy and tDCS in children with CP. We will conduct a 2-arm parallel clinical trial to investigate the effect of a combined application of tDCS and hydrotherapy.

**Methods and analysis::**

This study is an outcome assessor and data analyst-blinded, randomized, controlled superiority trial during the period from October 2021 to December 2023. CP patients meeting the inclusion criteria will be allocated in a 1:1 ratio into the treatment group (hydrotherapy plus tDCS), or the control group (treatment as usual). All participants will receive 30 sessions of treatment over 10 weeks. The primary outcomes will be the difference in the Gross Motor Function Assessment and Pediatric Balance Scale during rest and activity. The secondary outcomes will be the difference in adverse effects between the control and treatment groups.

**Conclusions::**

This study aims to estimate the efficacy of a combined application of tDCS and hydrotherapy in patients with CP.

**Trial Registration::**

This study protocol was registered in Chinese ClinicalTrials.gov, ID: ChiCTR2100047946.

## Introduction

1

Cerebral palsy (CP) is a neurodevelopmental disorder caused by a brain injury resulting in poor coordination and motor control deficits, which is one of the most widespread physical deformity in children.^[1]^ This disorder commonly occurs in 2.11 cases per 1000 live births and are widely recognized for causing dystonia, motor, and movement dysfunction, and intellectual disability.^[2,3]^ A previous meta-analysis demonstrated that the prevalence of CP among children aged 0 to 6 years in China is 0.23%.^[4]^ The European surveillance of CP group described the motor type of CP as spastic, dyskinetic (dystonia, chorea, and athetosis), ataxic and mixed types involving the mentioned types.^[5]^ Spastic cerebral palsy is the most common type of this movement disorder, which occurs in more than 80% in children.^[6]^ CP is usually diagnosed in childhood, but its course can last into adolescence, adulthood, and has different severity. There are evidences that children with CP have a higher rate of deterioration of physical and mental function and a higher risk for secondary diseases.^[3,7]^ It is reported that the cost of care for each child is estimated at $921,000 in the US.^[8]^ CP brings a heavy burden on families and society and becomes a significant public health issue.^[9]^

The conventional treatment for children with CP is made up of medical treatment, physical therapy (PT), occupational therapy, psychotherapy, surgical therapy, virtual reality technology, hyperbaric oxygen therapy, stem cell transplantation, and speech therapy.^[10–12]^ Almost all these treatments are aimed at improving patient activity and functional participation, however, none of them can completely cure CP. In recent years, PT as a treatment for CP is developing rapidly, which is a special treatment method based on physical factors such as sound, electricity, light, force, water, magnetism, and thermal power. Owing to the risks of neurosurgery and side effects of pharmacological intervention, PT becomes the central part of rehabilitation for children with CP.^[13,14]^ Among them, hydrotherapy promotes children's voluntary and passive movement in the water through the resistance, buoyancy, static pressure, and warming effects of water, which is beneficial to improve human blood circulation and relax the muscles of the whole body, thereby promoting the alleviation of muscle spasm and the reduction of muscle tension, and then improves the children's balance ability, expands the joint range of motion.^[15]^ Numerous studies have pointed out that the potential of hydrotherapy programs have significant benefits for children with CP.^[15,16]^ The result of a 10-week aquatic exercise training program is effective in the functional rehabilitation of children with spastic CP.^[17]^ A previous systematic review published in 2017 suggested that evidence on aquatic interventions for children with CP is limited since only 2 used randomized control trial design, and the results were mixed.^[18]^ Another systematic review published in 2021 showed that hydrotherapy can help improve the motor function and activities of children and adolescents with CP, and may improve their quality of life, which included 9 randomized controlled trials (RCTs).^[19]^

Noninvasive brain stimulation is one of PT which is under active investigation in childhood neurology and psychiatry, especially in disorders where focal cortical over- or under-activation is part of the pathophysiology.^[20]^ Among them, 2 are developing rapidly, they are transcranial magnetic stimulation and transcranial direct current stimulation (tDCS). tDCS constant electrical currents are conducted to the brain via scalp electrodes, which is undergoing investigation as a credible treatment for a series of neuropsychiatric diseases. This technique shares a capacity to modulate regional cortical excitability, and well-tolerated by children and adults.^[21,22]^ Now, active tDCS research is pushed in part by a favorable tDCS safety profile, the low cost of tDCS stimulator, and by fairly repeatable effects on the cortex, where (coarse) exposure to cathodal current brings about cortical suppression and exposure to anodal current brings about cortical activation.^[23]^ tDCS has been tested as a treatment for several pediatric neurologic conditions.^[20,22]^ Several RCTs also reported a beneficial effect of tDCS in patients with autism spectrum disorder,^[24]^ attention-deficit/hyperactivity disorder,^[25]^ epilepsy^[26]^ and CP. The finding from a meta-analysis suggested that tDCS can improve the static balance in children with CP at follow-up and have a positive effect on gait velocity.^[27]^ The heterogeneity of participant characteristics, dosing parameters, and outcome indicators makes it difficult to integrate citations and directly apply them to clinical practice. Caution must be taken when using this summary as an implementation guide.^[27]^ The Commenter of this meta-analysis suggested that researchers could reduce heterogeneity, increase sample size, avoid unnecessary repetition of additional pilot studies as positive results have been confirmed, and establish a focus on immediate and longer-term participant-centered efficacy outcomes while closely monitoring safety, so that future research will be more meaningful to clinicians.^[28]^

To sum up, when hydrotherapy and tDCS are used to treat separately, it has positive therapeutic effect in children with CP. The development of new therapies in combination with physical rehabilitation approaches is critical to optimize functional outcomes. tDCS has attracted interest in this context, as significant functional improvements have been demonstrated in individuals with brain injuries after a short period of cerebral stimulation. Since the onset of this work, tDCS has been used in combination with constraint-induced therapy, gait and mobility training, virtual reality therapy to potentiate the treatment effect.^[29–31]^ Up to now, there are no studies on the effect of a combined application of hydrotherapy and tDCS in children with CP. We will conduct a 2-arm parallel clinical trial to investigate the effect of a combined application of tDCS and hydrotherapy. We hypothesized that tDCS combined concurrently with hydrotherapy would result in the greater and longer-lasting improvement in motor function.

## Methods and analysis

2

### Study design

2.1

This study is an outcome assessor and data analyst-blinded, randomized, controlled superiority trial and will be conducted at the Second Affiliated Hospital of Qiqihar Medical University, from October 2021 to December 2023. CP patients who meet the inclusion criteria will be allocated in a 1:1 ratio into the treatment group (hydrotherapy plus tDCS, n = 75, expected), or the control group (treatment as usual, n = 75, expected). All participants will receive 30 sessions of treatment over 10 weeks. The study design is presented in Figure 1.

**Figure 1 F1:**
[figure not shown]
CONSORT flowchart demonstrating the progress of 2 groups through the randomized controlled trial phases. tDCS = transcranial direct current stimulation.

### Participants

2.2

Participants meeting the following inclusion criteria will be included: CP patients between 4 and 14 years old, CP was diagnosed according to the Subspecialty Group of Rehabilitation of Chinese Medical Association,^[32]^ voluntary participation and informed consent signed. Participants with any of the following exclusion criteria will be excluded: visual, auditory, and mental disorders affecting the results assessment; children with epilepsy who are uncontrolled with medication; skin problems such as open wounds or active infection; receiving botulinum toxin injections or surgery no earlier than 6 months before project start; participation in another clinical trial; unconscious, behaving strangely or uncontrollably, and are prone to medical accidents during treatment.

### Sample size

2.3

The necessary sample size has been estimated based on study of Whitehead et al,^[33]^ which estimated the minimum sample size of a pilot randomized trial with a continuous outcome variable. A previous RCT protocol about the effect of bilateral anodal tDCS vs treadmill training on brain activities of children with CP also used this Sample size estimation method. In our study, the Gross Motor Function Measure (GMFM) score which is a continuous outcome variable, is regarded as a primary outcome. The result is that 150 children with CP will undergo intervention or control group and will be assessed just once during pretest assessment to consider their results as a reference value for later comparisons. However, there is a lack of official pediatric reference values in GMFM of study on the combination of hydrotherapy and tDCS. Compared with the results of a meta-analysis, the sample size of our study is larger than that of each RCT on tDCS.^[34]^ Therefore, generalization of reference values from this study should be made with caution.

### Randomization

2.4

The participants will be assessed for the first time, pre-intervention, and then randomly assigned to one of the 2 groups: combination treatment group (treatment with hydrotherapy and tDCS), control group (treatment as usual). The randomization sequence will be distributed by numerically sequenced and sealed opaque envelopes. This process will be completed by an independent researcher.^[35]^ A second independent number performed the randomization. A series of numbered, sealed, opaque envelopes will be used to ensure concealed allocation. Each envelope will contain a card stipulating to which group the child will be allocated. This study will use the blind statistical analysis, where the statistical data will be analyzed by statisticians with unclear grouping and its meaning.

### Evaluation and follow-up

2.5

Two experienced physical therapists who blind to which group each child belongs will evaluate the both group in the evaluation procedures. Four evaluations will be conducted:

First evaluation: 1 week before intervention;Second evaluation: 1 week after the last intervention;Third evaluation: 4 weeks after the last intervention;Fourth assessment: 12 weeks after the last intervention.These evaluations will be conducted on 2 nonconsecutive days.

### Outcome measures

2.6

We will evaluate the CP children using questionnaires at the beginning of the treatment, within 1 week after 10 weeks of therapy, 4 weeks, and 12 weeks after the last intervention. Descriptive measures and characteristics, such as age, gender, body weight, type of CP and the outcomes were recorded for all study participants. All patient related data will be safely collected and stored. Only researchers related to the study will be allowed to access to the trial dataset. The primary outcomes of this study are Gross Motor Function Assessment and Pediatric Balance Scale (PBS) between the treatment group and the control group. The secondary outcomes are the difference in Pediatric Evaluation Disability Inventory (PEDI), adverse effects between the control and treatment groups.

#### Primary outcomes measures

2.6.1

Gross Motor Function Measure 88 (GMFM-88): The GMFM-88 will be used to detect gross motor function change in this study.^[36–38]^ The GMFM-88 is made up of 5 dimensions that can be analyzed separately or combined to produce a total GMFM-88 score. The 5 dimensions are as follows: lying and rolling, sitting, crawling and kneeling, standing, and walking, running, and jumping. All items are scored on a 4-point scale, the higher the score, the better the function.^[36–38]^ The treating therapist, in collaboration with parents and children, will choose Gross motor goal dimensions while considering the age of children and gross motor function classification system level. All evaluation process will be recorded and later scored by a senior physiotherapist who is blind to group allocation. The results will be reported as percentage scores.

PBS: The same blinded researcher will administer the PBS before and after the intervention.^[39–41]^ To assess balance, the PBS will be used, which is composed of 14 items. The items assess the functional activities which children could perform to function within the home, school, or community safely and independently. This scale has also been tested for children with CP and has good test–retest and interrater reliability when used assess participation of school-age children with mild to moderate movement disorder.^[39–41]^

#### Secondary outcome measures

2.6.2

The (PEDI, the PEDI is a questionnaire that quantitatively measures functional performance. This questionnaire includes 3 areas: self-care, mobility, and social function. The self-care part contains food, personal hygiene, toilet use, clothing, and toilet control. The functional items of mobility offered information about transfers, walking indoors and outdoors, and use of stairs. The social function part mirrors matters related to communication, problem solving, interaction with partner, amongst others. We will calculated total scores for each scale in each area, where each item has a score of 0 (the child is unable to play an activity) or 1 (the activity is part of the child's repertoire), and the sum of the items generates the score for each field.^[42,43]^

Adverse effects. We set this standard to refer to the specific details of previous study.^[35]^ Children with CP will be asked to answer on a 3-point scale: I did not feel unwell at any moment during the session; I felt unwell at some points during the session; I felt unwell throughout the session. The specific unwell are as follows: tingling sensation, burning sensation, headache, pain in the region where the electrodes were positioned, drowsiness, and mood swings. When participants pointed that they have specific adverse effect, in other words, the response is “2” or “3”, they will be instructed to quantify the intensity of perception (1, weak; 2, moderate; 3, strong; or 4, unbearable).

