#### Control group: usual care

2.7.1

Both groups of participants will continue to receive “usual care” during the 10-week intervention. Usual care refers to any therapeutic treatment or service that the child would normally receive outside of the intervention study. The researcher will evaluate children's condition, we expected that most participants in this study will not access additional therapy as possible.

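### The between-arm difference in adverse effects rests on a scale about the session and the electrode site, which has no defined counterpart in the usual-care arm

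*Protocol article*

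**What the plan says.** Section 2.6 (Outcome measures) sets the comparison: "The secondary outcomes are the difference in Pediatric Evaluation Disability Inventory (PEDI), adverse effects between the control and treatment groups". In the Abstract, the difference in adverse effects is the only secondary outcome named.

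Section 2.6.2 gives the one instrument. The child chooses among three answers. The first two read "I did not feel unwell at any moment during the session; I felt unwell at some points during the session", and the third is for discomfort that lasted the whole time. The symptoms covered are "tingling sensation, burning sensation, headache, pain in the region where the electrodes were positioned, drowsiness, and mood swings". A response of 2 or 3 leads to a four-point intensity grade.

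Section 2.7.1 describes the control condition: "Usual care refers to any therapeutic treatment or service that the child would normally receive outside of the intervention study". This care is not specific to controls: "Both groups of participants will continue to receive “usual care” during the 10-week intervention". The same section expects most participants to have little additional therapy.

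Electrodes and stimulation appear only in section 2.7.2, under the treatment group. That section schedules tDCS three times a week for 30 treatments and pool exercise twice a week for 10 weeks. No sham is described. The Abstract and section 2.1 nevertheless say that every participant has 30 treatment sessions over the 10 weeks.

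**The concern.** A difference between arms needs the same question, about the same kind of period, answered in both arms. Here the question is tied to an event (a session) and a body site (under the electrodes) that the article describes for one arm only.

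Two consequences follow. For the electrode-site item, usual care offers nothing to ask about. For headache, drowsiness and mood swings, which children can have without any study treatment, treated children report against a session while control children have no stated period to report against. Ordinary background symptoms could then appear as harm of the combination, or the control data might not exist at all.

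This is the only safety outcome described, in children aged 4 to 14 receiving a combination that the Introduction says has not been studied. The GMFM-88 and PBS comparisons are not affected.

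**Working it through.** The article states no figure for this outcome, so there is none to reproduce. The check sets the passages side by side and then sizes one scenario.

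**1. What each arm can answer**

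| Element of the scale | Treatment arm (2.7.2) | Control arm (2.7.1) |
|---|---|---|
| Session | tDCS 3 × 10 = 30; pool 2 × 10 = 20; 50 in all | None described; the Abstract and 2.1 say 30 for everyone |
| Electrode site | Yes | No electrodes, no sham |
| Tingling, burning | Can be asked | Can be asked in principle, but no reference period given |
| Headache, drowsiness, mood swings | Can be asked | Can be asked, but no reference period given |

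With 75 expected per arm, the treated arm has 75 × 30 = 2,250 tDCS sessions and 75 × 20 = 1,500 pool sessions scheduled.

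**2. Does the statement of 30 sessions for all restore the comparison?** Thirty equals the tDCS count of the treated arm. Suppose controls also had 30 sessions of some kind, and assume an equal risk of 1% per session, independent between sessions. The chance of at least one report is 1 − 0.99^k:

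- k = 30: 26%
- k = 50: 39%

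If reports are counted per child over all scheduled sessions, the arms differ through the number of occasions alone. The electrode item still has no control counterpart.

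**3. One scenario for the size of the problem.** Assumptions, none of them in the article: controls are coded as having no discomfort; the endpoint is any report per child; the test is a two-sided Fisher exact test at 0.05. The arm size of 75 and the 0.05 level are the article's; it does not state whether the level is two-sided.

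Fisher p against 0/75:

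- 5/75: 0.058
- 6/75: 0.028
- 8/75: 0.006

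Six reports are therefore enough. If a symptom truly affects the same share of children in both arms but is recorded only in the treated arm, the chance of a significant result is P(Binomial(75, rate) ≥ 6):

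| Assumed rate in both arms | Controls fixed at zero | Both arms asked alike |
|---|---|---|
| 5% | 17% | 1.5% |
| 10% | 77% | 2.7% |
| 15% | 98% | 2.9% |

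The last column is the Fisher false-positive rate with the same true rate recorded in both arms of 75.

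**4. What the treated arm alone can show.** With 0/75 reports, the exact two-sided 95% upper limit is 1 − 0.025^(1/75) = 4.8%.

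**The case against.** The strongest reply is that the article does give controls sessions: the Abstract and section 2.1 say that all participants have 30. Usual care can itself include therapy sessions, and section 2.6.2 addresses the scale to children with CP without restricting it to one arm. Non-specific symptoms can be asked of controls, and the control version of a form is a detail that a condensed article may leave to the full protocol.

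Part of this stands. A reader might infer that controls have exactly zero sessions, that their answers must be either missing or fixed at no discomfort, and that the plan will therefore declare a false harm about 77% of the time. The documents do not support that. They contradict themselves on control sessions, they do not say how control answers are coded, and they do not reduce the scale to yes or no per child. Section 2.8 names no Fisher test: it lists chi-square for baseline characteristics and ANOVA or Kruskal-Wallis for treatment effects. The 77% belongs to one scenario at one assumed background rate.

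It would also go too far to call the electrode item meaningless. Without electrodes the risk in controls is zero, so the treated-arm rate is itself the excess risk. It is a usable description, and only a test against controls adds nothing.

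The reply does not restore the comparison. The wording that the article does give ties the answer to a session and an electrode site, and nothing in it defines a control session.

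**Conclusion.** The point holds as a mismatch between a stated outcome and its stated instrument. The electrode-site item cannot be compared between arms, and headache, drowsiness and mood swings have no equivalent reference period in controls. This rests on the text alone and needs no assumed rate.

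The size of any bias is not known. Under the scenario in step 3 it runs from 17% to 98% spurious significance as the assumed background rate goes from 5% to 15%; if controls are asked the non-specific items over a matching period, that bias largely disappears. The effect is confined to a secondary outcome, so the point should be corrected but does not threaten the primary comparisons. Separately, the statement of 30 sessions for all participants and section 2.7.1 must be reconciled.

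**What to change.** - In sections 2.6 and 2.6.2, make the session scale a tolerability outcome of the treatment arm. Report, per symptom, the number and percentage of children and of sessions with response 2 or 3, with exact 95% confidence intervals per child. Delete the between-arm difference for this scale.
- Limit any between-arm comparison to symptoms that both arms can have, such as headache, drowsiness and mood swings. Ask them with identical wording and an identical recall window in both arms, at the evaluations already scheduled in sections 2.5 and 2.6. Those fall before treatment and after its end, so the window must reach back into the same 10-week period in both arms if symptoms during treatment are to be captured.
- Reconcile the statement on 30 sessions (Abstract, section 2.1) with section 2.7.1, and say what, if anything, a session means for a control child.

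The cost is rewording plus a few questions at existing visits; no extra contacts are needed. The between-arm safety comparison then covers fewer symptoms and relies on recall.

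### The between-group comparison of adverse effects uses a question about a tDCS session that has no defined counterpart in the usual-care arm

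*Protocol article*

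**What the plan says.** The abstract states: "The secondary outcomes will be the difference in adverse effects between the control and treatment groups". Section 2.6 (Outcome measures) repeats the comparison alongside the PEDI, as "adverse effects between the control and treatment groups".

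Section 2.6.2 (Secondary outcome measures) describes one instrument. It opens with "Children with CP will be asked to answer on a 3-point scale", and the first answer is "I did not feel unwell at any moment during the session". The symptoms covered are "tingling sensation, burning sensation, headache, pain in the region where the electrodes were positioned, drowsiness, and mood swings". A child who reports one of them then grades its intensity from 1 to 4.

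Section 2.7.1 describes the control condition: "Usual care refers to any therapeutic treatment or service that the child would normally receive outside of the intervention study". Section 2.1 (Study design), however, says of both arms: "All participants will receive 30 sessions of treatment over 10 weeks". Section 2.6 places the questionnaires at the start of treatment, within a week of the end of the 10-week course, and at two later follow-ups. It lists none during treatment.

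**The concern.** A between-group difference in adverse effects means something only if both arms are asked the same thing, about comparable periods, equally often. Here the question is framed around a session, and one item presupposes electrodes. The control arm has neither as described.

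At stake is a named secondary outcome, and the only one the abstract mentions. If the arms are asked unequally, the reported difference mixes any true harm with the amount of questioning. A reader could then take an excess of headache or drowsiness in treated children for an effect of the intervention when it only reflects how often they were asked.

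**Working it through.** **Step 1. The passages side by side.**

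- *Contrast:* control against treatment (abstract; section 2.6).
- *Frame of the question:* the session (section 2.6.2). No frequency of asking is given, and the question is not limited to one arm.
- *Items:* six symptoms. One, pain at the electrode site, needs electrodes. The other five can be asked of any child.
- *Control condition:* care outside the study (section 2.7.1). Section 2.7.2 calls the absence of current for the rest of the session a valid control procedure, but that sentence sits in the treatment-arm text and gives controls no sham.
- *Sessions:* 30 for everyone (section 2.1). Section 2.7.2 gives tDCS 3 times a week, and 3 × 10 = 30, so the figure reproduces the tDCS course. Section 2.7.1 describes nothing for controls that would match it.
- *Timing:* four questionnaire time points (section 2.6), none during treatment. This does not fit a question about how the child felt in a session.

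These statements do not combine into one procedure that could be applied to both arms.

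**Step 2. What unequal asking could do (illustration).**

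Assumptions, none taken from the article: the background risk p per asking is the same in both arms; askings are independent; treated children are asked after each of 30 tDCS sessions; controls are asked at the 4 questionnaire time points; there is no true effect.

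The proportion ever reporting a symptom after k askings is 1 − (1 − p)^k. For p = 2%: 1 − 0.98^30 = 45.5% and 1 − 0.98^4 = 7.8%.

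| p per asking | Treated, k = 30 | Control, k = 4 | Difference (percentage points) | Control, k = 3 |
|---|---|---|---|---|
| 0.5% | 14.0% | 2.0% | 12.0 | 1.5% |
| 1% | 26.0% | 3.9% | 22.1 | 3.0% |
| 2% | 45.5% | 7.8% | 37.7 | 5.9% |
| 5% | 78.5% | 18.5% | 60.0 | 14.3% |

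The last column leaves out the time point at the start of treatment. With 75 children per arm, the first row means about 75 × 0.140 = 10.5 treated children against 75 × 0.020 = 1.5 controls.

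**Step 3. How far this depends on the assumptions.**

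If the same children tend to report repeatedly, the treated proportion is lower and the gap narrows. If controls are asked about a longer period than one session, their risk per asking is higher and the gap also narrows. With equal k and the same recall period the artefact disappears: 1 − (1 − p)^k is then the same in both arms. If controls are never asked, there is no comparator at all.

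**The case against.** The strongest reply is that the article does not exclude controls from the question. Section 2.6.2 speaks of children with CP in general, five of the six items need no electrodes, and section 2.1 gives everyone 30 sessions. That stands. A reader might infer that control children cannot answer the questionnaire; strictly, this holds only for the electrode-site item. The reply does not rescue the comparison, because section 2.7.1 places control care outside the study and no passage says what a control session is.

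It also stands that no frequency of asking is given. A reader might infer 30 askings, or 50 once the 2 × 10 = 20 hydrotherapy sessions are added, against none, with controls counted as symptom-free. The article says none of this. Children who were never asked would have missing data, not zeros.

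A reader might also infer that seizures and water-related events go unrecorded, since the list names neither and the exclusion in section 2.2 covers only "children with epilepsy who are uncontrolled with medication". That does not follow. The instrument is one tolerability scale, and a condensed article may leave general adverse-event recording to the full protocol.

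Nor is the main point merely missing detail of that kind. The article gives the scale, its answers, the symptoms and the grading, and this stated instrument does not fit the stated contrast and control arm.

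**Conclusion.** The point holds in a limited form. The comparison of adverse effects is not interpretable as written, because its instrument is tied to a tDCS session and the usual-care arm has no defined counterpart. Sections 2.1, 2.6, 2.6.2 and 2.7.1 must be reconciled.

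The conflict between these sections follows from the text alone. The size of any spurious difference does not. The range of 12 to 60 percentage points rests on the assumed risk of 0.5% to 5%, on 30 askings against 4, on independence and on equal risk per asking. It shows that the problem could be large; it does not predict what this trial would find. The two primary outcomes are not affected.

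**What to change.** 1. Report the tDCS session questionnaire as tolerability, descriptively, in the treatment arm only, and state when it is asked.
2. Base the between-group comparison on one treatment-neutral adverse-event question, asked in both arms at the same planned time points over the same recall period. Report the proportion of children with at least one event per arm, and the difference with a 95% confidence interval.
3. Reconcile the statement on 30 sessions for all participants with the description of usual care, and the questionnaire time points with a question about a session.

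The first change costs nothing. The second adds one short form. Parents should complete it, or unblinded staff already in the trial should handle it, because answers about the intervention could reveal the allocation to the therapists who assess the primary outcomes blind. Without a sham, families will know the allocation, so equal asking removes the artefact of frequency but not any influence of that knowledge on reporting. The report should say so.
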